### Statistical analysis

Descriptive statistics will be used to summarise the demographic and questionnaire data at baseline and follow-up. Means and SD for continuous and assumed continuous variables (eg, age and PROMs) and counts and percentages for categorical variables (eg, gender). Treatments for both the knee and weight management will be categorised according to NICE OA^37^ and obesity^38^ guidelines, offered and delivered and what proportion of participants complies with each of the treatment options as defined above.

A longitudinal linear regression model will be fitted using all available longitudinal data from participants with BMI ≥35 kg/m^2^ to determine the variables which predict the primary outcome (OKS) at 12 months after first presentation to secondary care. The explanatory variables will include those data collected at follow-up time points (EQ-5D, BMI change, adherence to treatments as described above, receiving TKR, BODY-Q score). In order to assess the veracity and stability of the fitted model, sensitivity analyses and a number of standard methods will be investigated for imputing missing values (eg, multivariate imputation by chained equations using mice package in R).^39^ All analyses will be performed in R with significance set at the 5% level.^40^

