### Sample size calculation

Previous studies at our centre predicting PROMs in knee pathology reported R² values, the proportion of the variance in outcomes accounted for by the explanatory data (ie, regression model terms), of approximately 30%. Using a more conservative R² of 20% (effect size=0.25), a sample size of 76 was estimated as required to achieve 90% power at a 5% significance level for a cross-sectional primary analysis at 12 months. For the longitudinal analysis (baseline, 6 months and 12 months), applying a design effect of 1.1 (assuming Intraclass Correlation Coefficient=0.05) increased the required sample to 84. Accounting for an expected 20% loss to follow-up, we aim to recruit a minimum of 105 participants with BMI ≥35 kg/m^2^ for the primary analysis.

In addition to the main cohort (BMI ≥35 kg/m^2^), baseline data will be collected from a comparator group with BMI <35 kg/m^2^. The original funding application assumed a BMI distribution of ~52% with BMI ≥35 kg/m^2^ and ~48% with BMI <35 kg/m^2^. However, early recruitment data indicate the actual clinical distribution is approximately 66% BMI <35 kg/m^2^ and 33% BMI ≥35 kg/m^2^. Based on this assumed split, we plan to recruit all eligible patients consecutively, regardless of BMI category, until a total sample of 400 is achieved. Given the expected split between those under and over the BMI threshold of 35 kg/m^2^, this should ensure we recruit approximately the required number of participants (n=105) for the primary analysis in the high BMI group. This sample size is consistent with the published guidelines for the planned exploratory modelling and hypothesis generation.^35 36^

This approach ensures that our final cohort will reflect the population presenting to secondary care, rather than enforcing an artificial quota by BMI category. While the comparator group of participants with BMI <35 kg/m^2^ will not be included in the primary analyses specified in this protocol, these data will be used for exploratory modelling and hypothesis generation. The study is therefore adequately powered for the planned analyses while remaining representative of the underlying clinical population.

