The findings from this study will help define which non-surgical strategies are currently used in routine practice and how patient-reported outcomes vary following these interventions. By examining associations between baseline patient characteristics, management pathways and subsequent outcome, this study will provide insight into which factors are associated with better or worse pain, function and weight-related outcomes over time. This evidence base will be critical for shaping future national guidelines aimed at reducing variation in care and supporting shared decision-making for people with obesity and knee OA. Future analyses may include advanced modelling techniques (eg, structural equation modelling) to explore relationships between baseline psychosocial, clinical and outcome variables, which will be piloted and refined as part of the wider project. These analyses form part of the overall study plan but will be reported separately from the main cohort results. Ultimately, the inter-related work packages in this study will deliver a substantial increase in our understanding of the experience and treatment of people with obesity and severe knee OA, particularly those who may not be able to access surgery, a common yet poorly understood challenge in current practice.

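### The 90% power belongs to an overall test that the model explains some variance, not to the stated task of determining which variables predict OKS

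*Protocol article*

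**What the plan says.** **Sample size calculation (Protocol article).** The calculation rests on R², described as "the proportion of the variance in outcomes accounted for by the explanatory data (ie, regression model terms"; that is, all terms together. It continues: "Using a more conservative R² of 20% (effect size=0.25), a sample size of 76 was estimated as required to achieve 90% power". The analysis named is cross-sectional, at 12 months. The number of model terms is not given. The follow-on step is "applying a design effect of 1.1 (assuming Intraclass Correlation Coefficient=0.05) increased the required sample to 84", and a 20% allowance for loss to follow-up brings the target to 105. The section ends by stating that power is adequate for the planned analyses.

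**Statistical analysis (Protocol article).** A longitudinal linear model in participants with BMI ≥35 kg/m² is fitted "to determine the variables which predict the primary outcome (OKS) at 12 months after first presentation to secondary care". The explanatory variables named are EQ-5D, BMI change, adherence to treatments, receiving TKR and BODY-Q. The only statement on error rates is "All analyses will be performed in R with significance set at the 5% level". The overall model test is not mentioned.

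**Status of the modelling.** The Abstract, the objectives and the opening of the Discussion use the language of exploring. The sample size section, however, says the BMI <35 kg/m² data "will not be included in the primary analyses specified in this protocol, these data will be used for exploratory modelling and hypothesis generation", which sets the primary analyses apart from exploratory work. Later the Discussion says of the expected results: "This evidence base will be critical for shaping future national guidelines aimed at reducing variation in care".

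**The concern.** Two different questions share one power statement. The sample size answers whether the terms, taken together, explain any variance in OKS. The analysis section asks which of them do. A sample large enough for the first can be well short for the second, because the assumed 20% of variance has to be divided among the terms.

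Two things are at stake. First, a real predictor could be missed and its absence read as evidence against it, on the strength of a 90% figure that was never about single variables. Second, if the coefficients are read one by one at 5%, a chance association (with one of the treatment variables, for example) could be listed as a predictor of the primary outcome.

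**Working it through.** **1. Reproducing the plan's figure.** Inputs from the sample size section: R² = 0.20, alpha = 0.05, power 90%.

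- Effect size: f² = R²/(1 − R²) = 0.20/0.80 = 0.25, as stated.
- Overall F-test of R² = 0 with u terms: noncentral F on u and N − u − 1 degrees of freedom, noncentrality f² × N.

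| Terms u | N for 90% power | Power at N = 76 |
|---|---|---|
| 5 | 72 | 0.920 |
| 6 | 77 | 0.899 |
| 7 | 81 | 0.877 |
| 12 | 99 | 0.766 |

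So 76 matches an overall test with about 6 terms, to within one participant. With the more conservative noncentrality f² × (N − u − 1), the nearest match is 5 terms (N = 78).

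- Design effect: 1 + (3 − 1) × 0.05 = 1.1; 76 × 1.1 = 83.6, rounded up to 84.
- Loss to follow-up: 84/0.80 = 105.

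The chain 76 → 84 → 105 is arithmetically sound. It is a calculation for the overall test only.

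**2. Power for a single term.** Assumption: p uncorrelated terms share the 20% equally. The partial effect size is then (0.20/p)/0.80, tested on 1 and n − p − 1 degrees of freedom with noncentrality equal to that effect size times n. For p = 6 and n = 84: (0.20/6)/0.80 = 0.0417, and 0.0417 × 84 = 3.5.

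| Terms p | Power per term, n = 84 | Power per term, n = 76 |
|---|---|---|
| 5 | 53% | 49% |
| 6 | 46% | 42% |
| 8 | 36% | 33% |
| 12 | 26% | 24% |

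Using n = 84 favours the plan, since the step from 76 to 84 is there to offset the design effect.

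**3. False predictors if each term is read at 5%.** The number of terms is not stated. Five is the count of variable groups in the Statistical analysis section and six is what N = 76 implies. Twelve results if these items each get a coefficient:

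- EQ-5D, BMI change and TKR (3);
- the two BODY-Q subscales (2);
- other knee surgery, physiotherapy and steroid injection (3);
- weight-loss surgery, weight-loss medication, structured or dietary programme, and exercise (4).

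*No variable predicts OKS (global null).* With independent tests the chance of at least one false predictor is 1 − 0.95^k: 22.6% for k = 5, 26.5% for k = 6, 33.7% for k = 8 and 46.0% for k = 12. Simulated regressions at n = 84, with predictor correlations of 0 to 0.6, gave 21–22% (k = 5), 32% (k = 8) and 43–44% (k = 12). The range is therefore about 21–46%.

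*Two terms are true predictors carrying the 20% R².* Simulation at n = 84, chance of at least one false predictor among the remaining terms:

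| Terms | Each term at 5% | Only after a significant overall F-test |
|---|---|---|
| 6 | about 18% | about 18% |
| 8 | about 25–26% | about 24–25% |
| 12 | about 38% | about 35% |

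Under the global null an overall-F gate holds the rate near 4–5%. Once some terms are truly associated, the overall test is usually significant and the gate removes almost nothing.

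**The case against.** The strongest reply is that this is an exploratory cohort study. The Abstract, objectives and Discussion speak of exploring associations, and the sample size section itself describes the sample as in line with guidance for exploratory modelling and hypothesis generation (whether that refers to the 105 or the 400 is unclear). Family-wise control is not normally required in such work, the 5% level is a conventional per-test threshold, and a journal article leaves gating and coefficient reporting to an analysis plan that is not shown.

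Much of this stands. A reader might infer that the plan breaks a promised 5% error rate and would declare a false predictor in 32–46% of studies. The article does not support that reading, for four reasons:

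- It promises no family-wise rate.
- It does not say in words that every term is tested at 5%; that is inferred from the stated aim and the 5% level together.
- The 32–46% needs about 8 to 12 terms, a count never given; the five named groups give 21–23%, and the six terms implied by N = 76 give 26.5%.
- It supposes that nothing predicts OKS, which is implausible when receiving TKR and same-time EQ-5D (with its mobility and pain items) are in the model.

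Nor is the absence of a multiplicity rule from a condensed article a defect in itself. The per-term power figures are also illustrations: a dominant predictor would have more power than shown and the others less.

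The reply does not rescue the power statement. That is something the article asserts, and its own inputs support it for the overall test alone. The exploratory status is also not applied consistently, since the article sets its primary analyses apart from exploratory modelling and gives them a formal alpha and power.

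**Conclusion.** The point holds in a limited form. The stated 90% power, and the conclusion that power is adequate for what is planned, apply to an overall test of R² with about 6 terms. They do not apply to finding individual predictors, which is the task the analysis section sets. On equal sharing among uncorrelated terms, power per term at n = 84 is roughly a quarter to a half, not 90%.

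The error-rate side is secondary and conditional on reading each term at an unadjusted 5%: about 21–46% for 5–12 terms if nothing predicts OKS, and about 18–38% for 6–12 terms with two true predictors. This is a correction to a stated power property and to the strength of one inferential claim. It does not show that the sample size arithmetic is wrong or that the cohort cannot meet its descriptive and exploratory aims.

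**What to change.** - **Sample size calculation:** state how many model terms were assumed for N = 76, and limit the 90% power statement and the closing adequacy claim to the overall R² test.
- **Statistical analysis:** replace the wording about determining which variables predict OKS with wording about estimating the association of each variable with OKS. Report individual coefficients as exploratory estimates with 95% confidence intervals, in line with the exploratory language of the Abstract, objectives and Discussion.
- **If individual predictors are to be declared significant:** state a multiplicity adjustment across terms, such as Holm. An overall-F gate alone is not enough, as the second simulation shows. Whether to go this way, or to name the overall test as the single primary test, is the sponsor's choice and not a necessary correction.

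**Cost.** Wording in the analysis plan and the results paper; no new data or participants. Recruitment ended on 19 December 2025, so 12-month follow-up runs to about December 2026 and the wording can be settled before those data are complete. The downside is that individual predictors can no longer be declared significant at an unadjusted 5%. Under Holm few would be likely to reach significance at this sample size (with 6 equal terms at n = 84, power per term at the first-step threshold of 0.05/6 is about 21%), which favours estimates with intervals.

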**Methods and analysis:**

This study will recruit 400 participants with severe Kellgren-Lawrence grade four knee osteoarthritis from eight secondary care centres in England. All participants, irrespective of BMI, will provide baseline clinical data and patient-reported outcome measures (PROMs), enabling characterisation of baseline associations between BMI, knee function and body image.

A prespecified subgroup of participants with BMI ≥35 kg/m^2^ (minimum n=105) will undergo longitudinal follow-up at 6 months, 12 months and 24 months, including repeat BMI measurement, PROMs and detailed data on access to surgical and non-surgical interventions, including weight-loss strategies and TKR. For those with BMI ≥35 kg/m^2^, statistical modelling will be used to explore associations between baseline factors and longitudinal outcomes including Oxford Knee Score and weight change at 12 months (n≥105). Structural equation modelling will be used to quantify associations between BMI and knee pain/function mediated by psychosocial factors using data from all participants (n=400). A nested qualitative study of surgeons and patients will explore obstacles and preferences in the management of severe knee osteoarthritis.

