### Baseline data collection

The baseline questionnaire will include:

Height and weight, which will be used to calculate BMI. This will be measured and recorded by a member of the research team or extracted from the electronic record if measured within the preceding 2 months.Oxford Knee Score (OKS), a patient-reported outcome measure (PROM) with 12 items, each of which is scored on an ordinal scale from 0 to 4 and totalled to give an overall assessment, that was developed for assessing outcomes after TKR.^17 18^ It has been extensively validated^19^,^21^ and its psychometric properties described previously^22^ and is the core measure used in the UK National Joint Registry (scoring 0–48; 0=worst possible score, 48=best possible score).OKS-Activity Participation Score (APQ) was developed as an adjunct to the OKS. The purpose of the APQ is to combat potential ceiling effect for OKS when used alone in a postoperative population^23^ (0=worst possible score, 100=best possible score).Body-Q, a PROM which was developed for use by people with obesity undergoing weight loss interventions. It measures four domains (appearance, eating-related concerns, health-related quality of life and experience of care). An international multidisciplinary consensus meeting identified which constructs were most important to measure and identified BODY-Q as the PROM instrument which best measured six out of eight of the most important domains.^24^ Two subscales will be used: body image and appearance-related psychosocial distress. For both subscales, 0=worst possible score, 100=best possible score (Rasch scaled scores).Euro-Qol-Five Dimensions-5 Levels (EQ-5D-5L) is a measure of health-related quality of life that assesses mobility, self-care, usual activities, pain/discomfort and anxiety/depression (five dimensions).^25 26^ The value set for England developed by Delvin *et al*^27^ will not be used as it was rejected by the National Institute for Health and Care Excellence (NICE).^28^ Instead, the scores will be mapped onto the 3L value set,^29^ unless the NICE guidance changes regarding this, reported as an index score −0.594 (worst score)–1 (best score) and anchored at 0 (death). A Visual Analogue Scale score (0=worst score, 100=best score) also forms part of EQ-5D-5L and provides a complementary patient-reported measure of overall health status.Generalised Self-Efficacy scale^30^: a questionnaire used to quantify a person’s perceived ability to cope with adversity, where 10=worst score and 40=best score.Hospital Anxiety and Depression Scale.^31^ A scale which quantifies depression and anxiety in medical patients. Scored from 0 to 21 for each of the anxiety and depression subscales, where 0=best score (no anxiety or depression) and 21=worst score (severe distress).

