
### Follow-up assessments

The follow-up questionnaire will collect data on participants’ weight, weight-loss treatments that participants have received and treatments for their knee and their outcomes.

At 6 months, 12 months and 24 months, the same PROMs collected at baseline (OKS, APQ, Body-Q, EQ-5D) will be readministered, with the addition of the Global Rating of Change Scale.^32^ This is a seven-point scale ranging from ‘no change or condition has worsened’ to ‘a great deal better’. This will provide a reference point against which changes in other PROMs can be interpreted, helping to distinguish meaningful improvement from measurement variability.

Participants will additionally be asked the following questions about previous knee treatments at each follow-up assessment: have they had a knee replacement or other knee surgery, physiotherapy and/or a steroid injection in the last 6 months and/or are they on a waiting list for knee replacement surgery.

Participants will also be asked about weight loss treatments including whether they have had weight loss surgery, taken prescribed medications for weight loss, attended an NHS-referred structured weight loss programme or dietary modification programme and/or they meet the minimum NHS-recommended exercise recommendations.

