## Discussion

This prospective cohort study will describe the baseline characteristics and PROMs of people with obesity and severe knee OA and explore whether these predict pain, function and weight change at 12 months. It will address a critical evidence gap in the non-surgical management of this population, who often face BMI-based restrictions to TKR by commissioners, individual hospitals or individual surgeons.

The inclusion criteria of BMI ≥35 kg/m^2^ target patients at the highest risk of poor outcomes and those most affected by commissioning restrictions, allowing us to explore the most clinically complex and underserved group. The strengths of this study include its multi-centre design, capturing practice across England, which will enhance the generalisability across the NHS. The follow-up period of 12 months will provide insight into both short-term and medium-term outcomes. In addition, participants have consented to long-term outcome collection to 24 months and through linkage with the NJR and HES, allowing ongoing monitoring of surgical interventions and healthcare utilisation beyond the study follow-up period. Long-term outcomes will be reported after completion of the main analysis in a separate publication. The use of validated PROMs alongside detailed treatment data will enable a nuanced understanding of patient journeys and inform modelling of predictors of functional outcomes.

The limitations of this study are that it will not be able to establish causal links between treatments and outcomes due to its observational design and the heterogeneity of treatment availability across sites. In addition, this study will not capture data on people with severe OA and obesity who are managed exclusively in primary care and are never referred to secondary care, limiting generalisability to this broader population. Anthropometric measures such as waist or knee circumference are not being measured, which will restrict the exploration of mechanistic or prognostic relationships.

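### The primary model enters follow-up EQ-5D and BODY-Q as explanatory variables for 12-month OKS, although both are outcomes readministered with it, which pulls the TKR and weight-change associations towards zero.

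*Protocol article*

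**What the plan says.** The Statistical analysis section describes one longitudinal linear regression in participants with BMI ≥35 kg/m², intended "to determine the variables which predict the primary outcome (OKS) at 12 months after first presentation to secondary care". It then names the explanatory variables: "The explanatory variables will include those data collected at follow-up time points (EQ-5D, BMI change, adherence to treatments as described above", and after that "receiving TKR, BODY-Q score".

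Three other places bear on this list:

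- **Timing.** Under Follow-up assessments, at 6, 12 and 24 months "the same PROMs collected at baseline (OKS, APQ, Body-Q, EQ-5D) will be readministered". EQ-5D and BODY-Q are therefore completed at the same assessments as the OKS.
- **Content.** Under Baseline data collection, EQ-5D "assesses mobility, self-care, usual activities, pain/discomfort and anxiety/depression". BODY-Q is limited to two subscales, on body image and appearance-related distress.
- **Purpose.** The Abstract says that "statistical modelling will be used to explore associations between baseline factors and longitudinal outcomes including Oxford Knee Score and weight change at 12 months". The Study aim section names baseline factors, treatments after recruitment and weight change as the candidates for predicting 12-month knee function. The Discussion says of the baseline characteristics and PROMs that the study will "explore whether these predict pain, function and weight change at 12 months". None of the three names follow-up EQ-5D or BODY-Q as a predictor.

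**The concern.** Two kinds of post-baseline variable are mixed in one list. TKR, other treatments and weight change are exposures that the objective wants related to knee function. Follow-up EQ-5D and BODY-Q are outcomes that those exposures may themselves change. EQ-5D is also in part a second reading of what the OKS measures.

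Conditioning on such a variable has two effects. It removes the part of the TKR or weight-change association that shows up as better mobility and less pain on EQ-5D. It also lets the model explain variance because one questionnaire resembles another. A reader of the results could then conclude that TKR or weight loss matters less than it does, and that health status is the main predictor of knee function.

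**Working it through.** **1. The plan's own sample size.** Inputs from Sample size calculation: R² = 0.20, 90% power, 5% level, ICC 0.05, three time points, 20% loss.

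- Effect size f² = 0.20/0.80 = 0.25, as stated.
- Overall F test with noncentrality 0.25 × N. The number of terms is not stated, so it was varied. N for 90% power is 72 with 5 terms, 77 with 6 and 81 with 7. The stated 76 corresponds to about 6 terms (power 89.9%).
- Design effect 1 + (3 − 1) × 0.05 = 1.1; 76 × 1.1 = 83.6, rounded up to 84; 84/0.8 = 105.

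The figures 76, 84 and 105 are reproduced. The sample-size arithmetic is not at fault.

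**2. Effect of adding a follow-up PROM.** Let T indicate TKR, and express both scores in within-group SD units:

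- OKS = d_O × T + e₁ and PROM = d_E × T + e₂, with corr(e₁, e₂) = ρ.
- Coefficient of T without the PROM: d_O.
- Coefficient of T with the PROM: d_O − ρ × d_E.
- Share lost: ρ × k, where k = d_E/d_O.

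The documents give neither ρ nor k. Assumed ranges are ρ = 0.3 to 0.8 and k = 0.5 to 1.0.

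| ρ | k = 0.5 | k = 0.75 | k = 1.0 |
|---|---|---|---|
| 0.3 | 15% lost | 22% | 30% |
| 0.5 | 25% | 38% | 50% |
| 0.7 | 35% | 52% | 70% |
| 0.8 | 40% | 60% | 80% |

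A simulation of 400,000 records per setting agreed with the formula to within 0.01 for ρ from 0.3 to 0.7. The row for 0.8 is from the formula alone. The same algebra applies to weight change. If k exceeds 1/ρ, the coefficient changes sign. That lies outside the assumed range, but it is conceivable for BODY-Q if body image responds to weight loss far more than the OKS does.

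**3. Effect on R².** Assume 40% operated (p) and a TKR effect of d = 1.5 SD. Then d² × p × (1 − p) = 2.25 × 0.24 = 0.54.

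- TKR alone: 0.54/1.54 = 0.35.
- TKR plus PROM: 1 − (1 − ρ²)/1.54, which gives 0.41 at ρ = 0.3, 0.51 at 0.5 and 0.67 at 0.7.

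The increase comes from the overlap alone. For scale, a single PROM correlating 0.45 with the OKS yields 0.45² ≈ 0.20, the whole R² on which the study was powered.

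**4. Room for a corrected model.** A list of 12 terms would need N = 99 at f² = 0.25 and 90% power. Then 99 × 1.1 = 108.9, rounded up to 109, and 109/0.8 = 136.25, or 137 recruits. That exceeds both the minimum of 105 and the roughly 132 expected (0.33 × 400). With 12 terms, power is 77% at N = 76 and 82% at N = 84. The replacement list must therefore be short.

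**The case against.** **Baseline factors.** A reader might infer that the model contains no baseline factor and so cannot address prediction at all. The documents do not support this. The list is introduced as what the variables include, not as a closed set, and the Abstract, Study aim and Discussion all name baseline factors. A condensed article may leave the full covariate list to the analysis plan.

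**Weight change as an outcome.** A reader might also infer that this outcome has no model. The Abstract says it will be modelled. The Statistical analysis section describes only the OKS model, which is again an omission an article may make. Using weight change as a predictor of OKS is what the objective asks for.

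**Timing.** No lag is fixed, and the follow-up time points include 6 months. It is therefore not stated that the 12-month OKS is regressed on the 12-month EQ-5D. This stands, but it does not remove the problem: a 6-month EQ-5D can still lie between an earlier TKR or weight loss and the 12-month OKS.

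**BODY-Q.** Its two subscales do not measure knee function, so the overlap argument is weaker. What remains is that it is an outcome that weight loss may change.

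**Size.** The correlations, effect ratios, proportion operated and effect size are all assumed, and the simulation omits baseline OKS and other covariates. This also stands. With covariates, ρ is the correlation that remains after adjusting for them.

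**Association only.** The article disclaims causal inference. That does not help, because the reported associations are themselves altered by the adjustment. Nor does an open-ended list help: an analysis plan that follows the article may add baseline terms but must still enter follow-up EQ-5D and BODY-Q.

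**Conclusion.** The point holds as a fault in what the article positively specifies. Followed as written, the primary model adjusts for follow-up EQ-5D, a partial re-reading of the outcome that lies downstream of TKR and weight change, and for BODY-Q, with less overlap. This is at odds with the predictors named in the Abstract, Study aim and Discussion.

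The direction is firm under two conditions: the exposure improves both measures, and they correlate positively given the exposure. The size is not known. The range of 15% to 80% rests wholly on the assumed ρ of 0.3 to 0.8 and k of 0.5 to 1.0, and no single value in it should be quoted as an estimate. The stronger readings set out in the objection, on missing baseline terms, a missing weight-change model and strict concurrency, are not part of this conclusion.

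**What to change.** In the Statistical analysis section:

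1. Remove follow-up EQ-5D and BODY-Q from the explanatory variables of the primary model and report them as outcomes. If a model containing them is wanted, present it as a labelled secondary analysis.
2. Where these constructs are wanted as predictors, use their baseline values.
3. State that the model contains baseline OKS and a short prespecified set of baseline factors, plus TKR, other treatments and weight change.
4. State the number of terms and keep it consistent with Sample size calculation. Baseline OKS, TKR, weight change and a single term for other treatments make 4, leaving about 2 baseline factors within the 6 that N = 76 supports. Each BODY-Q subscale and each separate treatment counts as a term. If about 132 participants were enrolled, then 132 × 0.8 ≈ 105 and 105/1.1 ≈ 95. That would support up to 10 terms (92 needed, against 96 for 11). A longer list needs the power statement revised.

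The cost is wording only, since all these variables are already collected, and a lower reported R². Recruitment closed on 19 December 2025, so the last 12-month assessments fall around December 2026. The change should be made before those data are analysed.
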